#### Recruitment

Recruitment of participants began in February 2017 and will continue through September 2019. Participants will be followed for up to two years with data collection to conclude by March 31, 2020. During program registration and within the first week of each program cycle, new participants (and parents/guardians if applicable) will be given information about the research study and the requirements of research participation. If the participant indicates interest, they (and the parent/guardian where applicable) will be taken through the consent process.

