## Methods/design

### Study design

The MLSE LaunchPad trial employs a single-arm, non-randomized within subject quasi-experimental design following a cohort of 350 participants aged 6–29 years old over up to 2-years of self-selected participation in programming at MLSE LaunchPad, a Sport for Development facility in downtown Toronto, ON, Canada. Data collection methods utilize repeated measures of age-specific outcomes according to hypotheses outlined in Table 1 and further described in Table 3 using self-reports and pedometer data at baseline, 6 months, 12 months, and 24 months from baseline. Qualitative assessments will take place annually throughout the data collection period using focus groups with a subset of participants. This protocol was developed in the fall of 2016 and initiated in February 2017. These data will collectively be used to evaluate the effects of intentional sport programming in a community hub on PYD and SFD outcomes in urban youth facing barriers. Moderating variables including age, gender, race, household income, postal code, program type, volume of participation and duration of participation will be explored to understand possible explanatory individual and programmatic elements of significance.

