#### Sample size

Based on the number of variables planned for analyses in each cohort (see Table 1) [43], we will recruit *n* = 150 youth ages 6–12, *n* = 100 youth ages 13–18 years of age, and n = 150 youth ages 18–29. Statistical power calculations were conducted to justify the appropriateness of the proposed study sample sizes for each age group. For youth aged 6 to 12, statistical power for the primary outcome variable, physical literacy, was analyzed using pre-post MLSE LaunchPad member data on the PLAYself Physical Literacy Assessment tool. To achieve a large effect size (Cohen’s d > = .8; MLSE LaunchPad participant mean = 1201, SD = 258.8; study group mean = 1277), the power calculation performed suggests that the proposed sample size of 150 will yield 94.9% post-hoc power. Power calculations were conducted using data previously collected at MLSE LaunchPad for primary outcome variables of interest in the 13 to 18-year-old cohort (i.e., self-esteem, grit, resilience, physical activity status, and physical activity levels). To achieve large effect sizes for these variables, the proposed sample size of 100 will yield 99.5–100% post-hoc power. Lastly, for youth aged 19 to 29, to achieve a large effect size in the primary outcome variable, employment status, the proposed sample size of 150 will yield 100% post-hoc power (power calculated using data collected at MLSE LaunchPad).

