#### Outcomes

Participants will complete a baseline assessment within 2 weeks of recruitment. Follow-up research assessments will take place at 6 months, 12 months, and 24 months from the baseline assessment with data collection concluding March 31, 2020. Outcomes have been identified based on the program theory illustrated in the MLSE LaunchPad Theory of Change (See Fig. 1). Outcomes and indicators for the primary objectives are detailed in Table 3.

**Table 3 Tab3:** Outcomes for Primary Objectives

Participants aged 6–12	
a) Increased physical literacy	Indicator:
	PLAYself Physical Literacy Assessment for Youth [36] 22-item graded self-report scale used to evaluate level of physical literacy
b) Physical activity minutes/day	Indicator:
	One-week pedometry producing at least 3 days of valid data with a minimum wear time of 10 h/day
c) Continued engagement in sport	Indicator:
	Self-report of regular sport/physical activity participation
Participants aged 12–18	
a) Life skills:	Indicator:
i. Critical Thinking ii. Resilience iii. Self-esteem iv. Self-regulation v. Social Competence vi. Grit	Critical Thinking in Everyday Life Scale [37] 20-item self-report Likert scale used to measure use of critical thinking skills including reasoning, enquiry, analysis/information processing, flexibility, and evaluation Child & Youth Resilience Measure [38] 12-item self-report scale used to measure ability to sustain well-being Rosenberg Self Esteem Scale [39] 10-item self-report Likert scale used to assess global self-esteem Motivation and Self-Regulation Subscale; derived from the School Attitudes Assessment Survey [40] 4-item self-report Likert scale used to measure ability to initiate and continue behaviours required to achieve academic goals Social Competence Scale for Teenagers [41] 9-item self-report scale used to measure positive social skills necessary to get along well with others and function constructively in groups Grit Scale [42] 8-item self-report scale used to measure stamina in dimensions of effort and interest
b) Academic Performance:	Indicator:
i. School Attendance ii. Academic Performance iii Academic Attainment	Self-report of number of missed school days over past two weeks measured as a percentage GPA as per last report card; failed courses marked as “R” on TDSB report cards will be input as 45% Self-report of highest grade/level completed
c) Physical Outcomes	Indicator:

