*Ages 13–18:* Repeated measures ANOVAs will be used to examine the main effect of time on positive health behaviours and each of the six life skills, controlling for demographic variables such as age, gender, household income and race. Moderation analyses will be used to explore the impact of program dosage on the relationship between time and each of the six life skills. Pearson’s product-moment correlation coefficients will also be used to explore the relationship between each of the life skills, positive health behaviors and academic outcomes. Logistic regression will be used to identify predictors of high school graduation for the subset of this age group that would be expected to graduate during the study with possible predictors including scores for each life skill at 2-year follow-up, program dosage and program type, while controlling for gender, household income, housing status and baseline life skills score. The same variables will also be used in a standard multiple regression to identify predictors of continued participation in sport and physical activity in this age group.

*Ages 19–29:* Repeated measures ANOVAs will be used to examine the main effect of time on rate of employment, apprenticeship, or continued training, personal income, and rate of continued participation in physical activity, controlling for demographic variables such as age, education level, household income at baseline and housing status at baseline. Logistic regression will be used to identify predictors of employment status at 2-year follow-up, which may include program type and program dosage (number of programming hours), while controlling for similar demographic variables as identified above for the Repeated Measures ANOVA.

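### Data collection closes on March 31, 2020, so only participants with a baseline by March 31, 2018 can have a 24-month assessment; the power statement, 2-year analyses and imputation rule make no allowance for this

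*Protocol article*

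**What the plan says.** Under Recruitment, the article gives the accrual window, "Recruitment of participants began in February 2017 and will continue through September 2019", and then the closing date: "Participants will be followed for up to two years with data collection to conclude by March 31, 2020". The Outcomes section repeats the closing date and sets the schedule: "Follow-up research assessments will take place at 6 months, 12 months, and 24 months from the baseline assessment". Baseline may come slightly after recruitment: "Participants will complete a baseline assessment within 2 weeks of recruitment". Study design describes the study as "following a cohort of 350 participants aged 6–29 years old over up to 2-years of self-selected participation".

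Sample size sets the cohorts at "150 youth ages 6–12", "100 youth ages 13–18 years of age" and a further 150 in the oldest group, and states power at those full numbers. For physical literacy in the youngest cohort it gives 94.9% with 150 participants.

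Data analysis plans repeated measures ANOVAs for the effect of time in all three cohorts. For ages 19–29 it adds "Logistic regression will be used to identify predictors of employment status at 2-year follow-up". For ages 13–18 it uses life-skill scores at the 2-year visit as predictors of graduation and of continued sport participation. For missing data, the amount and pattern are to be examined first, and single mean imputation is then applied where needed.

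**The concern.** Recruitment continues until six months before the study closes, while the last scheduled visit is 24 months after baseline. For most of the accrual window the 24-month visit falls after closure. It will be absent because of the enrolment date, not because of anything the participant does.

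Three parts of the plan depend on how many people can have that visit: the power figures, the analyses defined at 2 years, and the imputation rule. None of them refers to the closing date. Two things are at stake. First, any 2-year result will rest on a smaller, earlier-enrolled group than the stated sample sizes suggest. Second, if visits that were never due are handled as ordinary missing data and filled with a mean, a large share of the 24-month values would be constants, which understates variance and makes a change over time look more certain than it is.

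**Working it through.** **Inputs.** Accrual February 2017 to September 2019 and closure on March 31, 2020 (Recruitment). Visits at 6, 12 and 24 months, and baseline within 2 weeks of recruitment (Outcomes). Cohorts of 150, 100 and 150; PLAYself means 1201 and 1277, SD 258.8, stated power 94.9% (Sample size). Assumed, because the article does not give them: two-sided alpha 0.05, a one-sample (before-after) test, and the accrual pattern.

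**Calendar (no accrual assumption).** The window has 32 calendar months.
- 24-month visit: baseline by March 31, 2018, so February 2017 to March 2018 = 14 months; 14/32 = 43.75%. The other 18 months (56%) cannot yield one.
- 12-month visit: baseline by March 31, 2019, so 26 months; 26/32 = 81.25%.
- 6-month visit: just reachable for a baseline by September 30, 2019. A baseline up to 2 weeks after a late-September recruitment could miss it.

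Counting days and varying the start day, the end day and a 0 to 2 week baseline lag, the share of the window lost at 24 months is 55% to 59%.

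**Numbers reaching 24 months, if accrual were uniform, before dropout.** 0.4375 × 150 ≈ 66; 0.4375 × 100 ≈ 44; 0.4375 × 150 ≈ 66. In total that is 175 of 400, or about 153 of the 350 named under Study design.

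**Reproducing the stated power.** d = (1277 − 1201)/258.8 = 76/258.8 = 0.294. Power = Φ(d√n − 1.96). With n = 150: Φ(0.294 × 12.25 − 1.96) = 94.9%, which matches the article.

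**The same formula for a 24-month contrast, ages 6–12:**

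| Share enrolled by March 2018 (assumed) | n at 24 months | Power |
|---|---|---|
| 30% | 45 | 50% |
| 43.75% (uniform) | 66 | 66% |
| 60% | 90 | 80% |
| 80% | 120 | 90% |
| 100% | 150 | 94.9% |

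**Effect of mean-filling visits never due.** In a simulation of a paired baseline to 24-month t-test with no true change and 150 participants, the undue 24-month values were replaced by the observed 24-month mean. The nominal 5% error rate became about 28% with 45 observed, 19% with 66 and 13% with 90. The result hardly changed for baseline to follow-up correlations between 0 and 0.8.

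**The case against.** The strongest reply is that the truncation is disclosed. Both Study design and Recruitment say follow-up lasts up to two years, and the accrual and closing dates stand in adjacent sentences. That is fair, and variable follow-up is no fault in itself. But the disclosure is not carried into the sample size, the 2-year analyses or the imputation rule.

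Several further objections stand and limit the point:
- The accrual pattern is unknown. The 44% is a uniform-accrual figure, and strong early enrolment would shrink the loss.
- The article does not tie its 94.9% to a visit, and it names no 2-year analysis for ages 6–12. The analyses it does name at 2 years belong to the two older cohorts, for which it gives no inputs from which power could be recomputed. The graduation model is already confined to those expected to graduate during the study.
- The d of 0.29 comes from the article's means and SD, but the same sentence speaks of a large effect of at least 0.8. At d = 0.8 the formula gives over 99.9% power even with 45 participants. Only 0.29 reproduces the stated 94.9%, but the article does not resolve the contradiction.
- Imputation is conditional on an inspection of missingness, so it is not certain that undue visits would be filled. Nor does the article say that the ANOVAs will use complete cases only. The plan simply does not exclude either course.

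A reader might also infer that the 24-month group is made up of people from the facility's first year. The article gives no opening date, so the supported description is participants enrolled by March 31, 2018.

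**Conclusion.** The point holds. The calendar part is exact: 18 of 32 accrual months cannot give a 24-month assessment and 6 of 32 cannot give a 12-month one. The 2-year analyses can have the stated sample only if every cohort was full by March 2018, which the article does not say and which recruiting through September 2019 makes unlikely.

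The size is conditional. About 66, 44 and 66 participants at 24 months assumes uniform accrual and no dropout. Power of about 66% also assumes d = 0.29, a one-sample two-sided test at 0.05, and a 24-month physical literacy contrast. It should be read within the range of 50% to 90% for 30% to 80% enrolled by March 2018. It would be tempting to conclude that the trial's power is 66%, but the documents do not support that as a firm figure or as one for the whole trial. Nor do they show that 12 months must become the main comparison; that is a choice for the investigators.

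This should be put right before analysis, because it determines what the 2-year results can claim and whether mean imputation would inflate the false-positive rate.

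**What to change.** - State the expected number in each cohort at 6, 12 and 24 months given the March 31, 2020 closing date and actual enrolment by month.
- Restate power at those numbers, naming the visit and the test, and settle which effect size is meant.
- Treat any visit not due by March 31, 2020 as administratively censored. Keep it separate from missed visits in the missing-data tables and never mean-impute it.
- Label every 24-month and 2-year result as applying to participants enrolled by March 31, 2018.
- Optional: make the 12-month contrast the main before-after comparison. It still loses 6 of the 32 accrual months.

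The cost is revised wording and recalculated figures, with no extra participants. The price is that the 2-year claim and the stated power will look less favourable.

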#### Study setting

All programming and data collection will occur at MLSE LaunchPad, a SFD facility for youth facing barriers in downtown Toronto, Ontario, Canada. The facility includes 3 sport courts, a rock-climbing wall, 3 classrooms, a commercial kitchen, wellness rooms for confidential services, a large atrium, a staff room, and multiple offices and storage spaces. MLSE LaunchPad’s stated focus is on achieving sustainable, wide-ranging social outcomes for youth facing barriers through a SFD approach. All programs are free of charge and the facility offers programs for youth facing barriers aged 6–29.

The facility is located on the ground floor of a subsidized housing building. The local area has a high proportion of subsidized housing and the highest density of homeless shelters in Canada [33, 34, 44]. The area exhibits high rates of poverty and is home to a large number of low income families including over 3000 youth [35, 43, 45, 46]. Approximately 40% of the population was born outside of Canada and approximately 40% are racialized individuals, with black as the predominant racialized group [35, 43, 45]. The area is also considered to have serious safety issues, with a high rate of criminal activity [47].

#### Intervention

Programs (described in Table 2) include a mix of sport plus programs, developed by an in-house team of sport programmers, and plus sport programs, several of which have been developed collaboratively with community partner organizations with similar target demographics and intended PYD impacts. The collaborative programming model engages the expertise of the aforementioned community partner organizations; academic partners with knowledge of PYD and SFD; and partners in the broader sport and physical education sectors. Each program falls under one of the following program pillars: Healthy Mind, Healthy Body, Ready for School, or Ready for Work. All programs incorporate sport and physical activity as a part of a psychologically and physically safe learning environment. An evidence-based coaching philosophy creates consistent coaching standards across programs, ensuring that life skills teaching is explicitly incorporated into all programs and that peer-peer and peer-leader relationships are emphasized. Coaches delivering programs are trained in life skills development and transference and physical literacy and fundamental movement skills by academic partners to provide high-quality, evidence-based and intentionally designed youth SFD programming based on the program theory explicated in the MLSE LaunchPad Theory of Change (see Fig. 1). Youth mentors, who are present in the facility before, during and after program times, act as resources to participants and facilitate connections with peers, leaders, and community resources. Youth mentors play a key role in the teaching of life skills by modelling positive behaviours and using teachable moments and are considered a key element of programming for all 3 age groups.

**Table 2 Tab2:** Program Descriptions

Age	Available Programming	Expected Outcomes	Evaluation Tool
6–12	Learn to Play (Sport Plus) • Registered, structured 8-week program, 1x/week for 1 h • Coach led according to programming curriculum designed to build sport specific skills, general movement skills, and sport-specific knowledge • Minimal competition • Sport options: basketball, soccer, futsal, ball hockey, football, multisport, rugby, rock climbing, golf, lacrosse, dance, tennis, run club, adapted sport Open Gym (Sport Plus) • Unregistered, semi-structured sport program offered multiple times per week in 1-h blocks • Participant-directed learning that is supported by a coach to develop intrinsic motivation and autonomy, general movement skills, and participant-selected movement and/or sport skills Sport + Nutrition (Sport Plus) • Registered, structured 9-week program, 1x/week for 2 h • On-court physical activities, sports, and games of low organization, plus kitchen activities and nutritional education • Co-led by kitchen instructor and on-court coach • Designed to develop general movement skills, general kitchen skills, and understanding of health concepts (nutrition, physical activity etc.) PA Day Programming (Sport Plus) • Registered 1-day full-day program that includes sport and physical activity programming as well as off-court activities • Program runs on school holidays throughout the school year Day Camp (Sport Plus) • Registered 2-week full-day program that includes sport and physical activity programming as well as off court activities Plus Sport Program Partners • Quantum Sports Learning Association – Registered after-school academic support and athletic coaching program, 1 day/week for 2 h/session • Square Circle – registered after-school social circus program, 2 days/week for 2 h/session • New Leaf Yoga – unregistered after-school yoga program, 1 day/week for 1 h Homework Club Homework support is available from 4 to 6 pm 3 days/week	Increased Physical Literacy Increased Physical Activity Increased rates of participation in sport and physical activity	PLAYself 1-week pedometry Self-report of regular sport/physical activity participation All outcomes are also assessed through scheduled qualitative data collection
13–18	Learn to Play (Sport Plus) • Registered, structured 8-week program, 1x/week for 1 h • Coach led according to programming curriculum designed to build sport specific skills in tandem with a relevant life-skill, general movement skills, and sport-specific knowledge • Minimal competition • Sport options: basketball, soccer, futsal, ball hockey, football, multisport, rugby, rock climbing, golf, lacrosse, dance, tennis, run club, adapted sport League Play (Sport Plus) • Registered, structured program – duration is variable (5x/week for 1 week, 2x/week for 4 weeks, or 1x/week for 9 weeks) • Coach led including practice plans & game play, designed to build sport specific skills in tandem with a relevant life-skill, knowledge of sport-specific rules, tactics, and team play • Each program day includes practice time, a game, and a team meal • Sport options: basketball, soccer, ball hockey, multisport, volleyball Multi-Day School Field Trip (Plus Sport) • Structured 8-week program in collaboration with local schools • Classes attend 4 half-day sessions 1x/2 weeks • Program content is a blend of physical activity and workshop-style learning with two options: Sport + STEM (Science, Technology, Engineering and Math) and “Fuel for Fun” (nutrition and physical activity) • Concepts taught in programs are reinforced at school by the classroom teacher Boys’, Girls’, & Co-ed Leadership Camps (Plus Sport) • Registered, structured 5 day (1 week) full-day program • Coach led blend of on-court and off-court programming including sport-specific skills, general movement skills, teambuilding & leadership activities, and life skills Leaders-In-Training (Plus Sport) • Registered, structured 8-week full-day program (5 days/week) • Participants must apply • Program includes 2 weeks of job skills training and certifications, 5 weeks of coaching day camps, and 1 week of professional development field trips Open Gym (Sport Plus) • Unregistered semi-structured sport program • Participant-directed learning that is supported by a coach to develop intrinsic motivation and autonomy, general movement skills, and participant-selected movement and/or sport skills • Drop-in game play is available Plus Sport Program Partners: • Peacebuilders International – Registered restorative justice program, 3 h 1 day/week for 6 weeks; youth diverted from the court system participate in a blended off-court and on-court program that includes talking circles and complimentary physical activities as an alternative to sentencing • Pathways to Education Group Mentoring – Registered program, 3 h 1 day/week for 24 weeks; youth participate in a blend of off-court and on-court activities relating to themes such as identity and anti-oppression, communication and teamwork, and relationships • Pathways to Education Iron Chef – Registered program, 2 h 1 day/week for 8 weeks; youth participate in a blend of activities in the kitchen and on the court relating to food budgeting, food preparation, and healthy physical activity • SoCirc – Registered social circus program with a performance element, 3 h 1 day/week for 8 weeks	Increased Life Skills Increased Academic Performance Increased Health Behaviour Increased or continued sport and physical activity participation	Life Skills • Resilience (Child & Youth Resilience Measure) • Self-Esteem (Rosenberg Self-Esteem Scale) • Self-Regulation (Motivation and Self-Regulation Subscale from the School Attitudes Assessment Survey) • Social Competence (Social Competence Teen Scale) • Grit (Grit Scale) Academic Performance • Self-Reported School Attendance • Report Card • Self-Report of highest grade/level completed Health Behaviour • Healthy Behaviour Questionnaire • 1-week pedometry Self-report of regular sport/physical activity participation All outcomes are also assessed through scheduled qualitative data collection
19–29	Plus Sport Program Partners • NPower Canada – Classroom-based technical support professional training program that runs 5 half-days/week for 10 weeks with an on-court sport and activity component for 1 h/day 2 days/week • Covenant House – Kitchen-based hospitality placement training program that runs 5 full days/week for 8 weeks with an on-court sport and activity component for 1 h/day 2 days/week Open Gym (Sport Plus) • Unregistered semi-structured sport program • Participant-directed learning that is supported by a coach to develop intrinsic motivation and autonomy, general movement skills, and participant-selected movement and/or sport skills	Increased employment, apprenticeship, or training placement Increased rate of participation in sport or physical activity	Self-report of placement in job, apprenticeship, or training full- or part-time Self-report of regular sport/physical activity participation All outcomes are also assessed through scheduled qualitative data collection
All Ages	Events • One-time events providing specific demographic groups with novel experiences with specific intended outcomes, such as: - Empowering Girls through Sport - Kyle Lowry/Adidas event - Michael B. Jordan appearance - Community Celebration days (facility launch and anniversary celebrations) - Toronto Maple Leafs Prospect Camp - Toronto Maple Leafs “Next Gen” game - Toronto Maple Leafs and Toronto Raptors viewing parties - Basketball clinics - 3 on 3 basketball tournaments - MLSE game experiences Drop-in Counselling • Drop-in counselling with Child and Family Therapists • Therapists are available several hours each week in an on-site Wellness Room Snack Program • Fresh after-school snacks are provided 3 days/week for participants and their families	Outcomes relate to age-specific outcomes identified above	n/a

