A large, long-term longitudinal study investigating PYD outcomes in a SFD facility for urban youth facing barriers that is based on a clear theory of change illustrating program components is therefore needed. This research is important for both theoretical and practical reasons, and addresses several future research directives published in the field including calls for mixed-methods, longitudinal, and evaluative studies that validate the development of life skills through sport and evaluate the impact of program type of PYD outcomes [26, 30–32]. The current study proposes that participation in theory-based SFD programming at a dedicated facility will lead to increased PYD outcomes in urban youth facing barriers to positive development with age-specific objectives outlined in Table 1 and further articulated in Fig. 1, the Maple Leaf Sports and Entertainment (MLSE) LaunchPad Theory of Change. Repeated measures ANOVAs will be used to explore the effect of long-term participation in MLSE LaunchPad programming on age-specific outcomes. Moderation analyses will be used to identify the impact of program dosage on the relationship between time and primary outcomes. Finally, regression analyses will be used to identify the predictors of primary outcomes to better inform programming.

**Table 1 Tab1:** Study Hypotheses

Primary Hypotheses	
We hypothesize that participation in MLSE LaunchPad programming and wrap around services will result in:	
a) For youth aged 6–12:	• Increased physical literacy • Increased physical activity [28] • Increased rates of continued participation in sport or physical activity [33]
b) For youth aged 12–18:	• Increased positive health behaviors relating to physical activity, sleep, nutrition, smoking, substance use and sexual activity [29, 34] • Increased life skills including critical thinking, resilience, self-esteem, self-regulation, social competence and grit [26] • Increase academic outcomes including school attendance, academic performance and high school graduation rates [26, 34] • Increased rates of continued participation in sport or physical activity [34]
c) For youth aged 19–29:	• Increased rates of placement in employment, apprenticeship, or continued training [26, 29] • Increased personal income • Increased rates of continued participation in sport or physical activity [34, 35]
Secondary Hypotheses	

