#### Data analysis

Preliminary analyses will be conducted after 6, 12, and 24 months of recruitment. All statistical analyses will be completed using either SPSS versions 24/25 (IBM) or *R*. Missingness in data will be evaluated for amount of missing data and patterns in missingness. Based on the results of this evaluation, a single mean value imputation method will be applied as needed.

*Ages 6–12:* Repeated measures ANOVAs will be used to examine the main effect of time on physical literacy scores, self-reported physical activity and rates of continued participation in physical activity, controlling for demographic variables such as age and gender. Moderation analyses will be used to explore the effect of program dosage in terms of the number of programs attended over the course of participation in this study on the relationship between time and change in physical literacy. A similar moderation effect will be explored in the relationship between time and the change in self-reported physical activity levels. Pearson’s product-moment correlation coefficients will also be used to explore the relationship between physical literacy and physical activity levels. A standard multiple regression controlling for age, gender, household income and housing status will be used to identify predictive variables for each of the three primary outcomes. Potential predictors for the change in physical literacy include program dosage, type of program involvement (Sport Plus or Plus Sport), physical literacy score at baseline and physical activity level. Potential predictors for the change in physical activity level and rate of continued participation in sport or physical activity include program dosage, type of program involvement, physical activity level at baseline and physical literacy score.

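### Sport participation is a primary outcome in every cohort but is worded as both a gain and a continuation, and for ages 13–18 the Data analysis section names no test of the hypothesised increase

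*Protocol article*

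**What the plan says.** Table 1 places sport participation among the primary hypotheses of all three cohorts, in the same terms each time: "Increased rates of continued participation in sport or physical activity".

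Table 2 lists expected outcomes by age. At 6–12 the entry is "Increased rates of participation in sport and physical activity" and at 19–29 it is "Increased rate of participation in sport or physical activity". At 13–18 it is "Increased or continued sport and physical activity participation".

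Table 3, which the Outcomes section names as the place where primary outcomes and indicators are set out, labels the outcome "Continued engagement in sport" in each cohort. The indicator is always "Self-report of regular sport/physical activity participation". Assessments are at baseline and at 6, 12 and 24 months.

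The Data analysis section treats the cohorts differently:
- **6–12:** repeated measures ANOVA for a main effect of time on "rates of continued participation in physical activity, controlling for demographic variables such as age and gender". A multiple regression for predictors follows, and its candidate predictors include physical activity level at baseline.
- **13–18:** the ANOVAs cover health behaviours and the six life skills. Sport participation appears only as the outcome of a multiple regression for predictors.
- **19–29:** repeated measures ANOVA for a main effect of time on the rate of continued participation. The only predictor regression in this cohort concerns employment.

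**The concern.** A rise in the share of youth who take part in sport and the persistence of those who already take part are different quantities. The first uses everyone enrolled and compares visits. The second looks only at those active at the start and asks how many still are. A youth who was inactive and takes up sport adds to the first and does not enter the second. A youth active at both visits is no change in the first and a success in the second.

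The article moves between the two for one primary outcome and, at 13–18, joins them with 'or'. That matters most in this cohort, because no named test there holds the report to the hypothesised increase. The study has a single arm, so no comparison group would show that flat participation is being presented as a benefit.

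**Working it through.** **Step 1. Set the text side by side.**

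| Place | 6–12 | 13–18 | 19–29 |
|---|---|---|---|
| Table 1, hypothesis | increase in a rate of continuation | same | same |
| Table 2, expected outcome | gain | gain or continuation | gain |
| Table 3, outcome label | continuation | continuation | continuation |
| Table 3, indicator | regular participation, self-report | same | same |
| Data analysis, test of change | ANOVA, effect of time | none named | ANOVA, effect of time |
| Data analysis, predictor regression | yes, lists baseline physical activity level | yes, baseline participation not listed | none for this outcome |

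**Step 2. Which quantity does the time test fit?** Let Y be 1 if a youth reports regular participation at a visit and 0 if not (a yes/no item is an assumption; the article does not give the response format). A main effect of time compares the mean of Y across visits, which is the proportion of the cohort participating. Continuation is the mean of Y at follow-up given Y = 1 at baseline. It is a conditional rate at follow-up with no baseline value that is free to vary. So the test planned at 6–12 and 19–29 matches a change in proportion and not the continuation label.

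**Step 3. What does the 13–18 regression estimate?** It reuses the variables of the graduation model: life-skill scores at two years, program dosage and program type, controlling for gender, household income, housing status and baseline life skills. Baseline sport participation is not among them. The model asks who is participating, or continuing, at follow-up. It does not estimate change from baseline, and its associations may partly reflect who was already active at entry.

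**Step 4. How far apart can the readings be?** The article gives no participation, stopping or uptake rate, so there is no stated figure to reproduce and every rate here is assumed.

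Formulas:
- Follow-up proportion = p0 × (1 − stop) + (1 − p0) × start
- Continuation = 1 − stop

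A count example at n = 100, the planned 13–18 size, has 60 participating at baseline, 12 of them stopping and 12 others starting:
- Proportion: 60% to (60 − 12 + 12)/100 = 60%. Change 0, exact McNemar p = 1.0.
- Continuation among baseline participants: 48/60 = 80%.
- Uptake among the others: 12/40 = 30%.

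Other assumed transitions:

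| p0 | stop | start | Follow-up proportion | Net change | Continuation |
|---|---|---|---|---|---|
| 0.70 | 0.20 | 0.20 | 0.56 + 0.06 = 0.62 | −8 points | 80% |
| 0.50 | 0.20 | 0.20 | 0.40 + 0.10 = 0.50 | 0 | 80% |
| 0.90 | 0.15 | 0.30 | 0.765 + 0.03 = 0.795 | −10.5 points | 85% |

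A continuation rate of 80% to 85% is thus compatible with no net change or a net fall. The figures describe the same youth correctly, but only the net change answers a hypothesis of increase.

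**The case against.** The strongest reply is that only one thing is measured. The indicator is identical in every cohort and at every visit, and nothing limits it to youth active at baseline. Table 1 says the rate should increase, and two cohorts have a test across time. On that reading, 6–12 and 19–29 already have a change in proportion and only the labels are untidy. Table 2 describes programs, so its 13–18 entry is an expectation and not a decision rule. The exact item wording and the cut-off for 'regular' may properly sit in a fuller document. Most of this stands.

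It does not cover 13–18. The Background says in general terms that repeated measures ANOVAs will explore age-specific outcomes, but the Data analysis section, which assigns outcomes to tests cohort by cohort, gives sport participation only a predictor regression at 13–18. The health behaviour questionnaire, which is tested over time there, has a physical activity component, but Table 3 lists it separately from sport engagement. Nor does the reply explain why Table 3 itself uses the continuation label.

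A reader might go further and infer that the article holds three rival success rules in every cohort, so that one data set could be declared a success, no change or a decline. The documents do not support that. The 'or' wording occurs once, for one cohort, and is not stated as a success rule. The decline reading needs continuation scored only among baseline participants and tracked from 100% (in the count example, 12 stopping and none starting, exact p = 0.0005), and the text states no such denominator.

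**Conclusion.** The point holds in limited form. The wording of a primary outcome is inconsistent across Tables 1 to 3 and the Data analysis section. At 6–12 and 19–29 this is a mismatch between label and test, since the planned test already fits a change in proportion. At 13–18 it has substance: the Data analysis section names no test of the hypothesised increase, the regression omits baseline participation, and the expected outcome could be read as met when participation has not risen.

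The size cannot be given from the article. The net changes of 0 to −10.5 points alongside 80% to 85% continuation rest on assumed rates and a yes/no item, and show only that the quantities can diverge. The change should be made, but it does not invalidate the study.

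**What to change.** - In Tables 1 to 3 and the Data analysis section, define the outcome once: self-reported regular sport or physical activity participation among all enrolled youth in the cohort, at each visit.
- Test it as within-person change from baseline in all three cohorts, including 13–18.
- Bring the 13–18 expected-outcome entry in Table 2 into line with this definition.
- Add baseline sport participation as a covariate in the 6–12 and 13–18 participation regressions. The 6–12 model already lists baseline physical activity level, which is related but not the same variable.
- Report continuation among youth participating at baseline and uptake among those not participating as two separate descriptive rates.

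The cost is rewording of three tables and the analysis section, one added test and one added covariate in each of two regressions. The indicator is already collected at every visit, so no new data are needed. The downside is that the reported figure may look less favourable than a continuation rate.
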